**Trial Registration:**

Iranian Registry of Clinical Trials IRCT20220202053916N1; https://tinyurl.com/c8jxfw36

**International Registered Report Identifier (IRRID):**

DERR1-10.2196/51599

## Introduction

Obesity affects more than 650 million people worldwide [1]. The prevalence of obesity is estimated to have nearly tripled since 1975; it is predicted that by 2030, 1 in 5 women and 1 in 7 men globally, equating to more than 1 billion people, will be living with obesity [2]. This increase is consistent across sex and age groups, with more than half of women of reproductive age being classified as overweight (defined by a BMI≥25 kg/m^2^) or obese (BMI≥30 kg/m^2^) [3]. Overweight and obesity are significant risk factors for many noncommunicable diseases (NCDs), including hypertension, dyslipidemia, type 2 diabetes mellitus, coronary heart disease, stroke, and some cancers [1,3]. The World Health Organization classifies risk factors for NCDs into changeable behavioral factors and metabolic risk factors [4]. Modifiable behavioral risk factors include smoking, excess salt/sodium in the diet, harmful drinking, and insufficient physical activity. Metabolic risk factors include hypertension, overweight and obesity, hyperglycemia, and hyperlipidemia [5].

Exercise has many benefits, including improving the condition and sensitivity of the body and brain, enhancing mental health, improving heart function, increasing immunity, reducing anxiety, and preventing osteoporosis. Female obesity is associated with several adverse pregnancy outcomes, including miscarriage, hypertension, preeclampsia, and diabetes [6], leading to reduced fertility, mainly due to anovulation [2]. However, other factors also vary between women with obesity and those with a body weight in the optimal range, including having a harder time conceiving, even in the case of regular menstruation. The current cultural context of valuing speed, including a tendency toward fast food, fast communication, and working within the virtual space, challenges the long-term patience of modern humans, and this desire for instant pleasure is evident in all facets of life worldwide. This issue is also emerging in terms of physical activity and exercise, in which the general public seeks to reach the desired goal in the shortest possible time; this results in increasing caloric expenditure with increased physical activities along with greater nutritional restrictions [3].

The most popular training methods at present for improving maximal oxygen consumption (VO_2_ max) are circuit training (CT) and high-intensity interval training (HIIT), which are commonly adopted by the general population, health and fitness professionals, and physiologists [7]. CT is typically performed at a moderate or high intensity over a period of 30-50 minutes and involves a range of aerobic, body weight, and resistance exercises with minimal rest [8]. Low-volume HIIT is defined as “short intermittent bursts of vigorous activity, interspersed with periods of rest or low-intensity exercise” [7], which is usually prescribed at a workout intensity of 80% to 100% of the maximum heart rate [9].

Whole-body CT and low-volume HIIT consisting of 8- to 12-minute interval episodes, interspersed with similar recovery time, have been shown to improve cardiometabolic health and cardiorespiratory fitness. The American College of Sports Medicine (ACSM) recommends that individuals perform moderate exercise 5 times per week, vigorous exercise 3 times per week, or a combination of moderate and vigorous exercise 3-5 times per week [10]. However, the optimal exercise type for improving overall health remains unclear [11]. Caloric expenditure is a common measure that can be used to compare different implementation systems. However, there are still no adequate doses for the workout tailored to specific populations [7].

The ACSM also identified the top 20 fitness trends for Australia, Brazil, Europe, Mexico, Portugal, Spain, and the United States, featuring individual fitness trends, including weight loss and unique health goals [9]. The new guidelines for adults specify a target range of 150-300 minutes of moderate-intensity physical activity and 75-150 minutes of vigorous-intensity physical activity, which differs from the previous guidelines that focused on achieving at least 150 minutes of moderate-intensity activity or 75 minutes of vigorous-intensity activity per week. This change acknowledges that there is a range of physical activity that maximizes risk reduction for health outcomes; in the case of older adults, multicomponent physical activity is recommended that focuses on functional balance and strength training to increase functional capacity and prevent falls [12].

Designing an exercise program above the standard level of calorie expenditure, especially for sedentary people, can be challenging. High-caloric exercises could act as a double-edged sword; on the one hand, a reduction of adipose tissue brings benefits of reducing metabolic syndrome, while on the other hand, high-intensity activity can be accompanied by increased inflammation. The restriction of energy intake below the amount necessary to maintain weight, known as caloric restriction (CR), can extend the lifespan even for people with normal weight. CR significantly extended lifespan in various preclinical studies with animal models; moreover, CR of approximately 30% was shown to increase life expectancy in humans by 1-5 years [13]. Thus, individuals with higher metabolic rates tend to have shorter lifetimes [14].

The development of this hypothesis stems from the inverse association observed between the rate of metabolism of mammals (by body weight and per day) and lifespan [15]. Mechanistically, the rate of life theory is supported by the free radical theory of aging [16], which postulates that 1%-3% of the oxygen consumed in mitochondrial ATP production produces reactive oxygen species (ie, oxidative stress) [17]. Therefore, with more energy expended as a function of time (ie, with aging) or because of a high metabolic rate, there is a greater likelihood of oxidative damage to the cells and tissues [18]. Oxidative stress also disrupts many molecular and cellular structures and functions. Low physical activity exacerbates this mechanism by reducing mitochondrial function and oxidation capacity in cells and tissues. Physically, caloric excess and low physical activity increase the fat mass and cause declines in skeletal muscle mass, strength, and physical fitness [19]. During a 6-month pilot study at Pennington Biomedical, participants in both CR groups lost 10% of their body weight [20] with a 25% reduction in total fat mass and a 27% reduction in visceral fat [11], the fat deposit type most closely linked to the development of metabolic diseases [16].

Similarly, participants in a study conducted at the University of Washington achieved a 20% energy deficit by exercising or losing comparable weight, total fat mass, and a visceral fat mass [13]. Although short-term CR resulted in no change in low-density lipoprotein (LDL) or high-density lipoprotein (HDL) cholesterol, 2 years of CR induced significant and persistent declines in LDL cholesterol and triglycerides, increases in HDL cholesterol, and a decreased ratio of HDL to total cholesterol; decreases in systolic and diastolic blood pressure and mean blood pressure were also observed [14]. After 1 year, CR improved left ventricular function in healthy older adults, an advantage typically observed with exercise [9]. Furthermore, the level of systemic inflammation, as measured by the concentrations of interleukin-6, tumor necrosis factor-α, and C-reactive protein, appears to have strong correlations with survival and is an important determinant of longevity in centenarians [12].

Although loss of bone mineral density is common with weight loss, regardless of the method, CR did not affect total bone mineral content in young individuals with type 2 diabetes and was deemed to be a suitable approach for weight loss in the general population [11]. However, another study showed that bone mass decreased at clinically important sites of osteoporotic fractures, such as the hip, femoral neck, and lumbar spine, after the age of 16 years [15]. These reductions were only partially proportional to changes in nutrition, physical activity, or body composition (10%-31% association in a regression analysis). This intraindividual variability in bone loss emphasizes a need for regular, close monitoring of bone health for individuals consuming a CR-based diet [16].

At present, the most popular health trend in Iran is strength training with free weights, which occupies a high proportion of the fitness industry for 2024. Specifically, eight trends related to fitness activities have emerged, including strength training with free weights, low-cost gyms, dance-based workouts, outdoor activities, Pilates, body weight training, core training, and water sports. Weight loss exercise and training methods under group-training formats ranked among the top 10 most popular health and fitness trends nationwide. There is no association between the type of training method and comfort with modern technology. Health was ranked as one of the top 20 attractive goals across the country, which is also reflected in the increased interest in aerobic sports, body weight bearing, and step training among Iranian women [17]. Furthermore, reductions in fat-free mass were associated with older age, male sex, less activity-related energy expenditure, and higher baseline BMI, and were not influenced by protein intake (normalized to body weight) [21]. Despite the greater effects of CR on fat-free mass in men, CR was found to only influence aerobic capacity and leg strength in women [19]. However, it remains unclear how specific exercise programs might affect inflammatory, oxidative, and muscle damage variables in the body in women over 35 years old who are overweight. Therefore, in this study, we aimed to evaluate whether standard- and high-calorie-expenditure exercises that are applicable to women with a BMI falling in the overweight category (ie, 25-29.9 kg/m^2^) who have not previously exercised will induce different types of changes and if there is a training capacity for 12 weeks of high-calorie-expenditure training for these women, which constitutes a form of CR.

## Methods

### Study Design

This study was designed to assess the effect of a 12-week multimodal exercise program intervention under two different calorie-expenditure conditions (high=3000 calories/week vs standard=1200 calories/week) and a no-exercise waitlist control group. The study was conducted at the University of Tabriz in the southeastern region of Azerbaijan, Iran. This study was registered in the Iranian Registry of Clinical Trials (IRCT20220202053916N1).

Figure 1 summarizes the proposed 12-week training plan. Participants will be allocated to three groups: a high-calorie-expenditure group, standard-calorie-expenditure group, and control group. In the high-calorie-expenditure group, participants will engage in 3 sessions of exercise per week for 45 minutes with an estimated expenditure of 650-900 calories per week for weeks 1 and 2. In the third week, they will also have 3 sessions per week with a training duration of 50 minutes per session at an estimated calorie expenditure of 750-1200 per week. In the fourth week, the duration of the exercise will be increased to 60 minutes with 3 sessions per week, thereby increasing the calorie expenditure of the exercise by approximately 1200-1300 per week. In the fifth and sixth weeks, the training time will increase to 70 minutes and the number of training sessions will also increase to 4 sessions per week, resulting in calorie expenditure of approximately 1800-1500 and 1600-2000 calories per week, respectively. In week 7, the training duration will increase to 4 sessions of 80 minutes each with estimated weekly calorie expenditure of 1800-2200. In weeks 8 and 9, the training duration will increase to 90 minutes with expenditure of 1900-2500 calories/week. In the last 3 weeks, the number of sessions will reach 5 with weekly sessions of 95, 100, 110, 110, and 110 minutes, respectively accounting for 2700-3100, 3000-3500, and 3300-3700 calories consumed in week 10, 11, and 12, respectively.

The standard-calorie-expenditure group will receive a 12-week exercise program in the form of 3 training sessions. In weeks 1 to 4, each session will comprise 40 minutes of exercise with 650-900 calories consumed per week; in weeks 5 to 8, sessions will last 60 minutes with 1000-1200 calories consumed per week; and weeks 9 to 12 will involve an increase in the training time to 80 minutes with expenditure of 1200-1500 calories per week.

The control group will not undergo exercise training, but will undergo the same blood tests, body composition measurements, appetite measurements, and nutrition and physical activity records as performed in the other two groups.

The schedule of data collection for the main outcome measures is presented in Table 1. Primary and secondary outcomes are measured 2 weeks prior to commencing the exercise training (baseline) and 2 days after completing the 12-week exercise or control period. We are also assessing the effectiveness of different types of exercise programs in mediating the risk of metabolic syndrome, including blood pressure disorders, increased blood lipids, uncontrolled blood sugar, obesity, and insulin resistance, with the goal of gaining a better understanding of the mechanism linking exercise to metabolic control. This is assessed by validating relevant formulas and other variables such as cardiovascular fitness and functional tests. Moreover, since high-calorie-expenditure exercise is associated with a goal of weight loss, there is a possibility that such a program will induce eating disorders, which is an issue that is more common in women. Therefore, two sessions were held for the participants to familiarize themselves with recording of daily food calories with the Eating Attitude Test-26 (EAT-26) questionnaire, including questions related to diet and appetite, in the 3 groups at 3 stages: before and during the course and at the end of the course. Body composition parameters were measured in the two training groups once every 2 weeks and in the control group before, in the middle, and at the end of the intervention. Blood parameters were also measured before and after the intervention to compare appetite levels. Performance tests were conducted before, during, and after the training period, and the calories consumed and physical activity were measured on a weekly basis.

**Figure 1 figure1:**
[figure not shown]
Study design and a summary of the proposed 12-week training programs for the two intervention groups and the control group. CG: control group; HC: high-calorie-expediture exercise; SC: standard-calorie-expenditure exercise.

**Table 1 table1:** Schedule of tests and measures for the primary and secondary outcomes.

Tests	Week											
	1	2	3	4	5	6	7	8	9	10	11	12
Blood sample	✓											✓
Functional test	✓					✓						✓
Appetite	✓					✓						✓
Body composition	✓		✓			✓			✓			✓
Physical activity	✓	✓	✓	✓	✓	✓	✓	✓	✓	✓	✓	✓
Nutrition	✓	✓	✓	✓	✓	✓	✓	✓	✓	✓	✓	✓

### Study Population

The program was designed for women who are classified as overweight (BMI=25-29.9 kg/m^2^) without an athletic background. Participants were recruited as a result of local media coverage related to fitness and health. To be considered eligible for this study, individuals had to be of female sex and aged between 35 and 50 years; informed written consent was required prior to the baseline measures and sample collection. The specific inclusion criteria are listed in Textbox 1.

Exclusion criteria are the onset of menopause during training, disruption of the menstruation cycle, and failure to participate in exercises in more than 30% of the sessions.

Inclusion criteria for study participation.In good health without a history of specific diseasesphysical diseases such as diseases and problems of the joints and bones or any type of physical and orthopedic injury to the extent that it would interfere with the implementation of exercises;endocrine and metabolic diseases (eg, type 1 or type 2 diabetes, kidney and liver thyroid diseases);cardiovascular diseases (eg, high blood pressure, coronary artery disease, atherosclerosis, peripheral vascular disease, heart disease);mental and psychological diseases (eg, depression, schizophrenia, mania);epilepsy;anemia;cancer;any infectious and inflammatory diseases.BMI of 25-29.9 kg/m^2^, leading to a classification of overweight.Inactive; participated in sports/fitness activities less than 3 times a week for less than 20 minutes in the past year and did not participate in organized activities in the past year.Premenopausal with a relatively regular menstrual cycle.Not taking any drugs that affect heart rate, metabolism, and body weight (such as drugs related to diabetes or thyroid diseases), antidepressants, nonsteroidal anti-inflammatory drugs, reproductive hormones, supplements, and vitamins.Have not consumed turmeric, caffeine, or alcohol 48 hours prior to each blood sample collection.Completed and signed the consent and engagement forms as well as medical history forms.

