### Sample Size and Group Allocation

The sample size was determined by a power calculation to detect group differences in the primary outcomes. Previous randomized controlled trials of exercise interventions have demonstrated effect sizes between 0.24 and 1.17 in similar populations for cognitive performance measures following aerobic interventions. To obtain 80% statistical power with an α level of .05, using an *F*-test for three independent groups and an effect size of 0.6, the sample size required was determined to be 30 participants using G*Power version 3.1. Among 60 applicants, a total of 33 participants have been recruited after primary evaluations, including height, weight, fat percentage, waist circumference, BMI, confirmation of the activities performed in the last year, and the lack of medical restriction to participate in the exercise training.

Following written informed consent of all participants and an explanation of the risks and benefits of the research, participants were randomized into the three groups: high-calorie-expenditure (n=11), standard-calorie-expenditure (n=11), and control (n=11) groups.

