### Limitations

This study has several limitations. The physical activity levels of the participants obtained with the IPAQ were not installed in the software and mobile phones of each participant. However, the results were determined to be satisfactory after answering the questionnaire. In addition, because this investigation started immediately after the lifting of restrictions related to the COVID-19 pandemic to conform with health protocols, it is possible that this long period of isolation had mental and psychological consequences on the participants.

When developing a target exercise interval, it is important to consider relevant variables to ensure that energy expenditure is at the level necessary for the health of all people. Further research is needed to confirm our results and determine the optimal group-based workouts that maximize caloric burn while increasing adaptation. In this study, we have confirmed the applicability of 5 high-calorie-expenditure training sessions in women over 35 years old, with benefits of weight loss, fat mass reduction, and muscle mass increase. In addition, our initial analyses suggest benefits with respect to inflammation and the lipid profile. However, the effects of these exercises on the immune system, bone conditions, reproduction, and other health facets remain unclear. It will also be valuable to examine the effect of this type of exercise over the longer term for 6 months to 1 year.

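### The exclusion criteria are events after randomisation, and the attendance rule cannot apply to controls; dropping these women from the analysis would bias the comparison and the applicability claim

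*Protocol article*

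**What the plan says.** The Study Population section gives three exclusion criteria: "onset of menopause during training, disruption of the menstruation cycle, and failure to participate in exercises in more than 30% of the sessions". The inclusion list in the same section already requires each woman to be "Premenopausal with a relatively regular menstrual cycle".

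Under Sample Size and Group Allocation, "participants were randomized into the three groups: high-calorie-expenditure (n=11), standard-calorie-expenditure (n=11), and control (n=11) groups". The size was set as follows: "To obtain 80% statistical power with an α level of .05, using an *F*-test for three independent groups and an effect size of 0.6", and "the sample size required was determined to be 30 participants using G*Power version 3.1".

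Study Design says "The control group will not undergo exercise training", although controls have the same measurements taken. The standard-expenditure arm trains three times a week throughout. The high-expenditure arm builds up from three sessions a week (weeks 1 to 4) to four (from week 5), and then "In the last 3 weeks, the number of sessions will reach 5".

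The Introduction ends by asking whether previously inactive overweight women have the capacity for 12 weeks of the high-expenditure programme. Limitations answers that "we have confirmed the applicability of 5 high-calorie-expenditure training sessions in women over 35 years old", and lists reproduction among the effects still unclear. The article does not say that an excluded woman stays in the analysis, and it gives no count of exclusions.

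**The concern.** An exclusion criterion normally acts before randomisation and so cannot disturb the balance between arms. Two of these criteria plainly act afterwards. The third, menstrual disruption, has no time attached, but a regular cycle is already required at entry, so a later event is the natural meaning.

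Three things are at stake:

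- **Comparability.** The attendance rule can take women out of the two exercise arms but never out of control. The trained women who remain are then a selected group set against an unselected one.
- **Applicability.** The trial asks whether these women can sustain the programme. Among women kept under an attendance threshold, everyone meets that threshold by construction.
- **Reproductive effects.** Menstrual disruption bears directly on an effect the article calls unclear. If it is a reason for removal and not a counted outcome, that evidence is lost.

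**Working it through.** **1. The plan's own sample size.** One-way F-test, k = 3, α = 0.05, effect size 0.6 taken as Cohen's f, noncentrality λ = N·f², df = (2, N − 3). At N = 30, λ = 30 × 0.36 = 10.8 and power is 0.8004. No smaller N reaches 0.80. The stated 30 is reproduced, so the calculation itself is not in question. With all 33 women, λ = 11.88 and power is 0.843.

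**2. Where the attendance rule bites** (Study Design schedule; weeks 8 and 9 taken as four sessions because only the duration is given there; the 30% rule read as missing more than 30%).

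| Arm | Sessions | 30% of sessions | Excluded when missed | Stops after week 9 |
|---|---|---|---|---|
| High | 4×3 + 5×4 + 3×5 = 47 | 14.1 | 15 or more | 15/47 = 31.9%, excluded |
| Standard | 12×3 = 36 | 10.8 | 11 or more | 9/36 = 25.0%, kept |
| Control | 0 | none | never | not applicable |

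If week 9 already has five sessions, as the time totals in Table 3 suggest, the high-expenditure figure is 15/48 = 31.3%, with the same result.

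This difference between the exercise arms is narrow. Stopping after week 8 excludes in both (19/47 = 40%; 12/36 = 33%). Stopping after the first session of week 10 keeps in both (14/47 = 29.8%; 8/36 = 22%).

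**3. Bias if excluded women are dropped.** Simulation with 11 women per arm, no true effect and 50,000 runs per setting. The k least adherent high-expenditure women are removed and the rest compared with all 11 controls. The documents give neither k nor the correlation r between adherence and outcome; both ranges are assumptions (k = 1 to 4, r = 0.3 to 0.7). The nominal one-sided false-benefit rate is 0.025.

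| Removed | Bias, outcome SD | False-benefit rate |
|---|---|---|
| 1 | 0.05 to 0.11 | 0.032 to 0.047 |
| 2 | 0.09 to 0.20 | 0.038 to 0.070 |
| 3 | 0.13 to 0.29 | 0.045 to 0.094 |
| 4 | 0.16 to 0.38 | 0.050 to 0.121 |

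**4. Power if losses fall only in the high-expenditure arm.** Equally spaced means d, 0, −d with f = 0.6 give d² = 1.5 × 0.36 = 0.54. With h women left in that arm and N = h + 22, λ = 0.54 × [(h + 11) − (h − 11)²/N].

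| h | λ | Power |
|---|---|---|
| 11 | 11.88 | 0.843 |
| 10 | 11.32 | 0.823 |
| 9 | 10.73 | 0.800 |
| 8 | 10.10 | 0.772 |
| 7 | 9.42 | 0.739 |

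**5. Feasibility denominator.** With 1, 2, 3 or 4 of 11 women failing the threshold, the proportion meeting it is 10/11 = 91%, 9/11 = 82%, 8/11 = 73% or 7/11 = 64%. Among the women retained it is 100% whatever happened.

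**The case against.** The strongest reply is that an exclusion criterion in a condensed article need not define the analysis population. A full protocol or SAP, neither of them shown, may analyse everyone randomised. That is possible. But the article states an exclusion and nothing shown reverses it, so an SAP that kept all 33 women would still have to be reconciled with this text.

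Several stronger readings are tempting, and the documents do not support them:

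- **That women were in fact removed.** No exclusion is reported; 11 per arm is the number randomised.
- **That none of the criteria can apply to controls.** This is true only of attendance. Controls have cycles and can reach menopause.
- **That the rule is generally harsher on the high-expenditure arm.** The exercise arms differ only for stopping points around week 9. For absences spread evenly over the course the limit is proportionally the same. If the 30% wording means attending too few sessions, the week-9 example fails, but the rule still acts after randomisation and still cannot touch controls.
- **That every exclusion favours the high-expenditure arm.** For menstrual disruption the direction is not shown. Affected women could be those who trained hardest.
- **That everyone unable to do the five-session phase is removed.** One session of that phase is enough to be kept (14/47). The pre-selection is real but incomplete.
- **That only weeks 10 to 12 reach the energy target.** Table 3 already puts week 9 at 3000-3200 kcal.
- **That power falls to 0.75 or 0.69.** Those values belong to 27 and 24 women analysed in balanced groups, that is 6 or 9 losses, and do not describe a few losses in one arm.

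**Conclusion.** The point stands in a conditional form. The stated criteria act after randomisation (for menstrual disruption, by inference from the entry criterion), and one of them cannot reach the control arm. If women meeting them are dropped from the analysis, as the text implies, the comparison with control is biased by about 0.05 to 0.38 SD for 1 to 4 high-expenditure women removed on adherence. That range rests on the assumed correlations and on no true effect. The loss of power, from 0.84 to between 0.82 and 0.74, is the lesser problem. The applicability statement would rest on women selected for attendance, and menstrual disruption would go uncounted although reproductive effects are called unclear. How far any of this has occurred cannot be told from the article.

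**What to change.** State that these events do not remove a woman from the analysis. Whether she continues training is a separate clinical matter and is not addressed here.

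- Analyse all 33 women in their assigned arms. Use week-12 data where obtainable and otherwise the repeated body-composition measurements already scheduled (Study Design, Table 1). Blood is sampled only before and after the intervention, so a missing final sample has no interim value behind it.
- Report attendance, and menstrual or menopausal events, by arm with 11 as the denominator.
- Base the applicability claim on all 11 women randomised to high expenditure.
- Label any analysis restricted to adherent women as a sensitivity analysis.

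The cost is mainly wording and reporting, and the article says analyses are still under way. The downsides are that the estimated effect may be smaller and that some week-12 data may be missing, since 12-week results are already reported and a late visit may no longer be possible.
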